### Statistical analysis

Categorical variables will be expressed as delivery rate when comparing baseline features between the SMART™ CONTROL and COMPLETE™-SE stent groups or the clopidogrel and cilostazol groups, and for categorical variables, comparisons between groups will use the chi-square or Fisher’s exact test. Continuous variables will be expressed as mean ± standard deviation, and for continuous variables, comparisons between groups will use the Student’s t-test. The primary and secondary endpoints will be analyzed using both intention-to-treat analysis (all subjects assigned to a treatment group) and per-protocol analysis (only subjects completed the treatment protocol). Study endpoints will also be analyzed per patient. For the primary endpoint (12-month binary restenosis rate) comparisons of the two patient groups will use the chi-square or Fisher’s exact test. At the end of the 12 months, cumulative restenosis rates will be calculated. All secondary endpoint analysis will be performed using the Student’s t-test, chi-square test, or Fisher’s exact test. Also, clinical outcomes such as revascularization of the target vessel, death, major cardiovascular events including myocardial infarction and cerebral infarction, and limb salvage rates will be analyzed using Kaplan-Meier survival estimates and a comparison of the groups will be performed using the log-rank test. A *P* value <0.05 is considered to be statistically significant. In order to evaluate the risk factors for recurrence, defined as restenosis or total occlusion, univariate and multivariate logistic regression analysis will be performed. Present research has concluded that there will be a very low chance of missing data to cause bias, and therefore, missing data for the major endpoints will be excluded from the analysis data. For repeated measurements for the secondary endpoints, last observation carried forward (LOCF) can be applied. The SPSS 20.0 (SPSS Inc, Chicago, Illinois, United States) statistics program will be used for all analysis.

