All ipsilateral iliac arterial lesions should be treated with angioplasty and/or stenting concomitantly and residual stenosis should be less than 50%. Treatment of tibioperoneal lesions is recommended only in cases of critical limb ischemia. There should exist at least one patent (<50% stenosis) tibioperoneal run-off vessel with good antegrade flow.

A final angiography will be performed after the intervention in both groups, with the use of the same angles and magnifications used in the baseline angiograms. Simultaneously, reference vessel diameter (RVD), minimal luminal diameter (MLD), percent diameter stenosis, and acute gain should be measured. The reference vessel diameter will be obtained from averaging 5-mm segments proximal and distal to the lesion. Technical success will be defined as the successful access and deployment of the stent and less than 30% diameter residual stenosis after the revascularization.

For the post-procedural medication, aspirin 100 mg and clopidogrel 75 mg will be administered once daily for one month. Then, patients of each group will be randomized by web-based randomization to receive either clopidogrel 75 mg or cilostazol 100 mg once daily in addition to aspirin 100 mg for at least 11 months in a 1:1 manner.

After enrollment and index procedure, clinical follow-up will be planned at 1, 6, and 12 months to evaluate clinical outcomes and ankle-brachial index score. Also, all patients will be recommended to have a follow-up catheter angiography or duplex ultrasound at 12 months according to local clinical practice. The incidence of stent fracture and binary patency will be assessed by plain X-ray and quantitative femoral angiography. The investigators will be urged to follow up on patients, either by office visits or by telephone contacts, as necessary. Patient adherence to the study drug and side effects will be checked and monitored at every outpatient visit. The decision of drug discontinuation will be discussed and checked under the physician’s recommendation.

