### Outcome measures

The primary endpoint of this study is the rate of binary restenosis (stenosis of at least 50% of the luminal diameter) or PSVR (peak systolic velocity ratio) ≥2.5 or 0 (PSVR = peak systolic velocity within the area of stenosis divided by peak systolic velocity in a normal adjacent proximal artery segment) in the treated segment at 12 months after the intervention as determined by catheter angiography or duplex ultrasound. The secondary endpoints are as follows: 1) composite of binary restenosis and major stent fracture (moderate or severe stent fracture); 2) stent fracture rate according to fracture grade (minor, moderate, severe); 3) limb salvage rate free of above-the-ankle amputation; 4) sustained clinical improvement rate at 12-month follow-up; 5) repeated target lesion revascularization (TLR) rate; 6) repeated target extremity revascularization (TER) rate; 7) total reocclusion rate; 8) comparison of angiograph variables consisting of late loss and restenosis rate; 9) ankle-brachial index (ABI) at 12 months; 10) the rate of major adverse cardiovascular events (MACE) composed of all-cause death, myocardial infarction, repeat percutaneous coronary intervention (PCI), and stroke at 12 months; 11) incidence of geographic miss during stent deployment due to jumping and/or elongation; 12) rate of binary restenosis or PSVR ≥2.5 or 0 according to clopidogrel and cilostazol; and 13) major bleeding rate between clopidogrel and cilostazol group. The detailed definitions are summarized in the Appendix.

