## Appendix

### Endpoints definitions

Binary restenosis: defined as a reduction in the luminal diameter of >50% according to the worst angiographic view at the narrowest site within the treated segment plus the 10-mm segments proximal and distal to the treated segment by catheter angiography or PSVR ≥2.5 (PSVR = peak systolic velocity within the area of stenosis divided by peak systolic velocity in a normal adjacent proximal artery segment) or total occlusion by duplex ultrasound. Stent fracture rate according fracture grade (minor, moderate, severe) [12]: plain X-ray examinations for the stent fracture are used or performed using at least two different angulations (30 to 45° difference) and the highest available magnification. Stent fracture is classified as minor (single strut fracture), moderate (fracture of more than 2 struts), or severe (complete separation of stent segments). Target lesion revascularization (TLR): defined as any repeat percutaneous intervention of the target lesion or bypass surgery of the target vessel performed for restenosis because of a return of ischemic symptoms, decrease of at least 1 Rutherford category, decrease in the ankle brachial index of >0.15, or restenosis of >50% as measured by catheter angiography. The target lesion is defined as the treated segment from 10 mm proximal to the stent and to 10 mm distal to the stent. Target extremity revascularization (TER): defined as any repeat percutaneous intervention of the target extremity or bypass surgery of the target extremity performed for restenosis because of a return of ischemic symptoms, decrease of at least 1 Rutherford category, decrease in the ankle brachial index of >0.15, or restenosis of >50% as measured by catheter angiography. Limb salvage: defined as survival free of amputation. Amputation is defined as above-ankle amputation of the index limb. Sustained clinical improvement rate [36, 37]: defined as persistent ABI value ≥0.15 and persistent improvement of ≥1 class according to Rutherford throughout follow-up when compared with baseline without the need for repeat TLR in surviving patients. Late loss: defined as a change in MLD from final angiogram to follow-up. Major adverse cardiac events (MACE): defined as composite of all-cause death, myocardial infarction, cerebrovascular stroke, and target lesion revascularization.

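### The completer per-protocol set is applied to bleeding, MACE and limb salvage; if completion includes the drug course, it can remove patients because of the event being counted

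*Protocol article*

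**What the plan says.** The Statistical analysis section sets two analyses for the same endpoints. The first is ITT: "The primary and secondary endpoints will be analyzed using both intention-to-treat analysis (all subjects assigned to a treatment group". The other, named later in that sentence, is a completer set: "per-protocol analysis (only subjects completed the treatment protocol". Neither analysis is called primary, and no endpoint is excepted from the second.

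The secondary endpoints under Outcome measures include three that matter here:

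- Endpoint 13: "major bleeding rate between clopidogrel and cilostazol group".
- Endpoint 10: "the rate of major adverse cardiovascular events (MACE) composed of all-cause death, myocardial infarction" and further components. The Appendix lists the MACE components somewhat differently, but all-cause death is in both versions.
- Endpoint 3, limb salvage. The Appendix defines it so that death is a failure: "Limb salvage: defined as survival free of amputation".

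On treatment, Randomization and interventions has a first month of aspirin and clopidogrel for everyone. Randomization to clopidogrel or "cilostazol 100 mg once daily in addition to aspirin 100 mg for at least 11 months in a 1:1 manner" follows. Stopping is foreseen: "The decision of drug discontinuation will be discussed and checked under the physician’s recommendation".

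**The concern.** Completion is known only after randomization, and the safety outcomes can determine it. Bleeding is an obvious reason to take a patient off an antiplatelet drug, and a patient who dies before the end of the course cannot complete it. A set defined by completion is then partly selected on not having had the event.

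The efficacy and safety of the two drug regimens is the trial's stated secondary purpose. Because the plan ranks neither analysis, a completer table of bleeding or MACE would stand beside the ITT table with equal status. A reader could take its lower rates, or a smaller or reversed difference between drugs, as evidence about safety.

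**Working it through.** **1. The plan's own figure.** Inputs from Sample size calculation: patency 65% and 80%, 5% significance level (taken as two-sided), 80% power, 1:1 allocation, 20% dropout. With pooled proportion 0.725:

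n = [1.96·√(2·0.725·0.275) + 0.842·√(0.65·0.35 + 0.80·0.20)]² / 0.15² ≈ 138 per group

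138 / 0.80 = 172.5, rounded up to 173; 2 × 173 = 346. Both stated figures are reproduced. Nothing below changes them.

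**2. Formula for the per-protocol rate.** Let r be the true event rate, f the share of event patients excluded as non-completers, and g the share of event-free patients excluded. Then

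PP rate = r(1 − f) / [r(1 − f) + (1 − r)(1 − g)]

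If f = g, the PP rate equals r and there is no bias. If f > g, it is below r. The protocol gives no bleeding, death or discontinuation rates, so r, f and g are all assumptions.

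**3. Size within one arm, with g = 10%.**

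| True rate r | f = 25% | f = 50% | f = 75% | f = 100% |
|---|---|---|---|---|
| 5% | 4.2% | 2.8% | 1.4% | 0% |
| 2% | 1.7% | 1.1% | 0.6% | 0% |

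Worked cell, r = 5% and f = 50%: 0.05·0.5 / (0.05·0.5 + 0.95·0.9) = 0.025 / 0.880 = 2.8%.

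**4. Size for the between-drug difference.** Assume true rates of 5% and 2% (difference 3.0 points) and g = 10% in both arms.

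| f, higher-rate arm | f, lower-rate arm | PP rates | PP difference |
|---|---|---|---|
| 10% | 10% | 5.0% vs 2.0% | 3.0 points |
| 50% | 50% | 2.8% vs 1.1% | 1.7 points |
| 80% | 40% | 1.2% vs 1.3% | −0.2 points |
| 40% | 80% | 3.4% vs 0.5% | 2.9 points |

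The difference disappears or reverses when event patients on the drug with more events are also more likely to be excluded. In the opposite pattern it hardly moves.

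**5. Death.** One month of common treatment plus at least 11 months of randomized drug reaches month 12, the end of planned follow-up. If completion means that drug course, f = 100% for death within 12 months. The death component of per-protocol MACE is then zero, and so are the deaths counted as limb-salvage failures. If completion means the stent procedure alone, later deaths stay in the set.

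**The case against.** The strongest reply is that ITT is required in the same sentence for the same endpoints. Every counted bleed, death or amputation in an assigned patient therefore stays in a planned analysis. The plan also has Kaplan-Meier and log-rank comparisons for death, major cardiovascular events and limb salvage, DSMB review of cumulative safety data, and committee review of all deaths. This stands, and it limits the point to the per-protocol tables.

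Second, the treatment protocol to be completed is not defined. The trial has two randomizations, and only endpoints 12 and 13 are tied explicitly to the drugs. For the stent comparison, completion could mean the procedure alone. This also stands, so the finding is conditional for MACE and limb salvage by stent. It is much weaker for endpoint 13, where the treatment being compared is a drug course and the criterion is completing it. The abstract speaks of one month for the drug comparison, whereas Randomization and interventions says "in addition to aspirin 100 mg for at least 11 months in a 1:1 manner". The two passages need to be reconciled. A shorter course would remove fewer patients, but by the same mechanism.

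Third, a full SAP may define the set more carefully. That would answer a complaint about missing detail. Here the article states a rule and applies it to all secondary endpoints.

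A reader might infer three stronger things that the document does not support:

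- *Per-protocol safety results are bound to be falsely reassuring.* A patient who has an event and stays on drug remains in the set, and the bias depends on f exceeding g.
- *Deaths vanish by definition from every per-protocol result.* This holds only if completion includes the drug course.
- *The plan is at fault for having no on-drug bleeding analysis.* That is normal SAP content. A bleed that leads to stopping occurs before the stop and is counted under ITT.

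**Conclusion.** The point holds in a limited form. A set of treatment completers is unsuitable for major bleeding, MACE, death and limb salvage, and the article applies it to them without ranking it below ITT. On the drug-course reading, it can understate bleeding, MACE and limb-salvage failure (so the salvage rate looks too high) and distort the comparison between drugs.

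The size cannot be fixed from the document. Under the illustrative assumptions it runs from no bias (equal exclusion), through a modest loss (5% shown as 4.2%), to complete loss of the events. A true 3.0-point difference between drugs could appear as anything from 2.9 points to slightly reversed in the asymmetric cases shown. The sample size is untouched, and the completer rule does not affect the ITT results. This should be corrected, but it does not threaten the trial's main conclusion.

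**What to change.** In the Statistical analysis section:

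- Restrict the completer per-protocol analysis to restenosis and other efficacy endpoints.
- Name ITT, on all assigned subjects, as the basis for major bleeding, MACE, death and limb salvage.
- State that dying, or stopping drug because of an event, removes no patient from a safety analysis.

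An on-treatment analysis may be added as supportive for endpoint 13 only. It should not replace ITT for MACE, death or limb salvage. Counting only from the first randomized dose to shortly after the last would drop first-month events, and also deaths or amputations well after stopping, which brings back outcome-related exclusion.

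The required change costs a sentence or two of analysis wording and leaves the sample size as it is. The optional analysis needs drug start and stop dates. The article plans adherence checks at every outpatient visit but does not say that these dates are recorded. Its small downside is that it is not protected by randomization, so it must be shown beside ITT.

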Diagnostic angiography will be performed in two different views at least 30 to 45° apart to evaluate the structure of the lesion. Femoropopliteal and tibial arteries will be visually checked for the presence of distal lesions. To document the precise location of the lesion and the site of the intervention, we will recommend the use of a ruler. In cases of total occlusion, both intraluminal and subintimal methods of recanalization will be allowed. In procedure, the use of other special devices will be allowed; for example reentry device OUTBACK™ catheter (Cordis Corp, Miami Lakes, Florida, United States) and Offroad catheter (Boston Scientific, Natick, MA, United states), CTO devices Frontrunner (Cordis Corp, Miami Lakes, Florida, United States) and Truepath (Boston Scientific, Natick, MA, United states), and atherectomy devices such as SilverHawk™ and TurboHawk™ (Covidien, Plymouth, Minnesota). After the successful passage of the guidewire, predilation of the target lesion with an optimally sized balloon will be performed prior to stent implantation. Recommended, minimal balloon dilation time is 120 seconds. Then, if there is a residual pressure gradient of ≥10 mmHg, residual stenosis of ≥30%, or flow-limiting dissection, the balloon angioplasty results will be considered as suboptimal results. Subsequently, web-based randomization for stent selection will be performed. Patients will be stratified into two groups, less than 15 cm or more than 15 cm, according to lesion length. Random allocation of the patients will be performed via a web-based computerized program separately managed at the Cardiovascular Intervention Research Institute (CIRI), Korea University Guro Hospital, Seoul, Republic of Korea. Patients will be randomized in a 1:1 manner according to two different stents (SMART™ CONTROL versus COMPLETE™-SE). The stents will be implanted to extend 10 mm proximally and distally from the margins of the target lesion with luminal narrowing of ≥50%. Spot stenting or full lesion coverage will be decided at physician’s discretion. When multiple stents are required, the margins of the stents should be overlapped by at least 10 mm. Adjuvant post-dilation after the stenting will be performed strictly within the stented segment, with up to 10% oversizing of the post-dilation balloon.

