### Statistical analysis

#### Sample size calculation

From previous studies, including ABSOLUTE [7], FAST [8], and ASTRON [9], recurrence rates in femoropopliteal lesions after one year were 32%, 34.4%, and 37%, respectively - approximately 35% on average. The recurrence rate for the SMART™ CONTROL stent was 34.8% in the SUPER-SL study - a multicenter, randomized controlled trial that compared two self-expanding nitinol stents, the SMART™ CONTROL and Luminexx stents, in femoropopliteal lesions [14]. So far, there are limited data on the one-year primary patency rate of the COMPLETE™-SE stent. Based on previous research results, the SMART™ CONTROL stent group will be the control group, and the COMPLETE™-SE stent group will be the experimental group. Based on the SUPER-SL results, the one-year primary patency of the SMART™ CONTROL stent is estimated to be 65% and the one-year primary patency of the COMPLETE™-SE stent is estimated to be 80%, which is higher than that of the SMART™ CONTROL stent. Recurrence will be defined as more than 50% restenosis or total occlusion under invasive angiography, or if invasive angiography is not performed, PSVR ≥2.5 when evaluated with duplex ultrasound. The statistical significance level is set at 5%, the power of test is set as 80%, and the randomization ratio is set as 1:1. Test for proportion and chi-square method are used. Using standard sample size formula, it was calculated that 138 patients per group are needed for a total of 346 patients, after accounting for a 20% dropout rate.

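### Stent randomization is stratified by lesion length, but the primary test and the 12-month ABI comparison ignore the stratum: valid, yet mildly conservative and less efficient than a stratified analysis

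*Protocol article*

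**What the plan says.** Under Randomization and interventions, the stent allocation is stratified: "Patients will be stratified into two groups, less than 15 cm or more than 15 cm, according to lesion length". The antiplatelet allocation comes later and is made inside each stent group: "Then, patients of each group will be randomized by web-based randomization to receive either clopidogrel 75 mg or cilostazol 100 mg once daily".

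Under Statistical analysis, the primary comparison is named outright: "For the primary endpoint (12-month binary restenosis rate) comparisons of the two patient groups will use the chi-square" or Fisher's exact test. The rule for the other endpoints is equally explicit: "All secondary endpoint analysis will be performed using the Student’s t-test, chi-square test" or Fisher's exact test. Secondary endpoint 9 in Outcome measures is "ankle-brachial index (ABI) at 12 months", a continuous variable, so it is assigned to the t-test. The one regression model in the section has a different purpose: "In order to evaluate the risk factors for recurrence, defined as restenosis or total occlusion, univariate and multivariate logistic regression analysis will be performed". It is not the treatment comparison.

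The sample size section uses the same unstratified chi-square method.

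**The concern.** Stratified randomization balances the arms on lesion length. If length predicts restenosis, that balance removes between-stratum variation from the stent difference. A test that ignores the strata still counts that variation in its standard error. Its true type I error is then below the nominal 5%, and it has less power than a test that uses the strata.

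The article gives reasons to think length is prognostic. The Background reports higher restenosis after balloon angioplasty when lesions exceed 10 cm, and restenosis that stays high in long lesions in the nitinol stent era.

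Two neighbouring points follow the same logic. The antiplatelet comparison ignores the stent groups within which it is randomized. The ABI comparison ignores the pre-procedure ABI, which has to be measured because Immediate outcomes in the Appendix defines hemodynamic success as a change from it.

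Because the tests are named, this is a stated choice and not a detail left to an analysis plan.

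**Working it through.** **1. The plan's own sample size.** Inputs from Sample size calculation: patency 65% versus 80% (restenosis 35% versus 20%), significance level 5% (taken as two-sided), power 80%, ratio 1:1, dropout 20%. The pooled formula has mean restenosis 0.275:

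n = [1.960·√(2·0.275·0.725) + 0.842·√(0.35·0.65 + 0.20·0.80)]² / 0.15² = 137.9, so 138 per arm.

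138/0.80 = 172.5, so 173 per arm and 346 in total. Both stated figures reproduce, and power at 138 per arm is 80.0%.

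**2. Type I error of the crude test.** Let s be the share of long lesions, g the restenosis gap between strata, and p = 0.35 under no difference. With exact balance within strata, the share of outcome variance lying between strata is

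ρ = s(1−s)g² / [p(1−p)],

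and the crude test has true α = 2[1 − Φ(1.960/√(1−ρ))]. The article does not give s or g. With s = 0.40 (assumed), s(1−s) = 0.24 and p(1−p) = 0.2275:

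- g = 0.10: ρ = 0.24·0.0100/0.2275 = 0.011, α ≈ 0.049
- g = 0.25: ρ = 0.24·0.0625/0.2275 = 0.066, α ≈ 0.043
- g = 0.375: ρ = 0.24·0.1406/0.2275 = 0.148, α ≈ 0.034

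**3. Power by simulation.** 138 per arm, balanced within two strata, marginal restenosis 35% versus 20%, a common odds ratio across strata, 40% long lesions. CMH is the Cochran-Mantel-Haenszel test.

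| Gap | Control restenosis, short / long | Crude α | Power, crude | Power, CMH | Gain |
|---|---|---|---|---|---|
| 10 points | 31% / 41% | 0.050 | 80.3% | 80.6% | 0.3 |
| 25 points (assumed) | 25% / 50% | 0.043 | 80.7% | 82.3% | 1.6 |
| 37.5 points (assumed) | 20% / 57.5% | 0.034 | 81.8% | 85.2% | 3.4 |

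Separate runs gave gains of 1.5 points at 25 and 3.6 points at 37.5. Changing the long-lesion share matters little. With 30% to 50% long lesions and 400,000 trials per setting, the gain is about 0.2 points at a 10-point gap, 0.8 to 1.0 at 20, 2.0 to 2.2 at 30, and 3.6 to 3.8 at 40. CMH α stays at 0.049 to 0.050.

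**4. Which gap does the article support?** Its only figures by length are 60% in general and 70% above 10 cm, after balloon angioplasty. That is a different treatment and a different cut from 15 cm. Read directly, the gap is 10 points. If 60% is an average over all lesions and 40% are long, the short-lesion rate is (60 − 0.4·70)/0.6 = 53.3% and the gap is 16.7 points. That is still below the 20-point setting, where the gain is at most 1.0 point.

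**5. ABI.** ANCOVA multiplies the residual variance by 1 − r², where r is the correlation of pre-procedure with 12-month ABI. At assumed r = 0.3, 0.5 and 0.6 the factor is 0.91, 0.75 and 0.64, a reduction of 9%, 25% and 36%. If the lesion-length stratum alone explains 1%, 5% or 10% of ABI variance (assumed), the crude t-test has α of 0.049, 0.044 or 0.039.

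**The case against.** The strongest reply is that design and analysis agree. The trial was sized with a crude chi-square for 80% power, and the crude test delivers at least that in every setting examined. The error is on the conservative side, so false positives are not inflated and the estimated difference is not biased. At the gap closest to the article's own figures the gain is a fraction of a point; only assumed gaps of 25 points or more make it visible. ABI is one of 13 secondary endpoints, the trial is not powered on it, and a t-test between randomized groups is valid. All of this stands. It sets the size of the point without removing it, because the better analysis uses information that is already collected.

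Three stronger readings should not be drawn:

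- **Power lost against plan.** A reader might infer that the trial falls short of 80%. It does not; the loss is only relative to a stratified test.
- **Operator choice at 15 cm.** A reader might infer that the operator picks the stratum for such a lesion. The article says allocation runs through a separately managed web program and gives the operator no such role. The boundary is a gap in wording.
- **Antiplatelet allocation stratified by length.** The article says only that this randomization takes place within each stent group. It does not mention lesion length there, so the design calls for stratifying that comparison by stent group and no more. No loss was quantified for this factor.

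**Conclusion.** The point holds as an efficiency improvement. The article fixes crude tests for a design stratified on a factor that it treats as prognostic. The cost is about 0.2 to 0.3 power points with α close to 0.05 at a 10-point gap, about 1.5 points with α about 0.043 to 0.044 at an assumed 25-point gap, and about 3.5 points with α about 0.034 at an assumed 37.5-point gap. These figures rest on 138 evaluable patients per arm, exact balance within strata, a common odds ratio and 40% long lesions; the share and the larger gaps do not come from the article. For ABI, the variance reduction of 9% to 36% rests on an assumed correlation of 0.3 to 0.6. The planned conclusions are not endangered.

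**What to change.** - **Primary endpoint:** make the main test a Cochran-Mantel-Haenszel test stratified by the lesion-length stratum used at randomization. Report the Mantel-Haenszel risk difference with its 95% confidence interval, and keep the crude chi-square as a sensitivity analysis.
- **Antiplatelet comparison:** stratify by stent group.
- **12-month ABI:** replace the t-test by ANCOVA with pre-procedure ABI and the lesion-length stratum as covariates.
- **Wording:** state which stratum contains a lesion of exactly 15 cm, matching what the randomization system already does, so that the live system is not altered.

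The cost is analysis wording only. No extra patients or data are needed, and 138 per arm and 346 in total stand. The article reports recruitment as ongoing, so the change can be specified before the outcome data are analysed.

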### Study population

Patients at least 20 years of age who have moderate or severe intermittent claudication or critical limb ischemia (Rutherford score of 2 to 6, except any patient who has undergone or plans to take major amputation) will be screened for study enrollment. A patient will be enrolled if they meet all of the inclusion and have none of the exclusion criteria. Inclusion criteria consist of clinical and anatomical criteria. The clinical criteria includes symptomatic peripheral-artery disease with moderate to severe claudication (Rutherford score of 2 to 3), chronic critical limb ischemia with resting ischemic pain (Rutherford score of 4), or chronic critical limb ischemia with ischemic ulcers (Rutherford score of 5 to 6), and patient must provide written informed consent. The anatomical criteria includes stenosis of more than 50% of, or occlusion of the ipsilateral femoropopliteal artery, patent (≤50% stenosis) ipsilateral iliac artery, or concomitantly treatable ipsilateral iliac lesions (≤30% residual stenosis), and at least one patent (less than 50% stenosis) tibioperoneal run-off vessel. Patients meeting any of the following criteria will be excluded from the study: failure to provide written informed consent; a history of major bleeding within prior two months; known hypersensitivity or contraindication to any of the following medications: heparin, aspirin, clopidogrel, cilostazol, or contrast agent; acute limb ischemia; previous bypass surgery or stenting of the ipsilateral femoropopliteal artery; untreated inflow disease of the ipsilateral pelvic arteries (>50% stenosis or occlusion); patients who have undergone major amputation (amputation of above the ankle) or major amputation is planned or required; patients with a life expectancy of less than one year due to comorbidities.

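### The planned Kaplan-Meier revascularization estimates treat death as censoring and would run slightly high; cumulative incidence with death as a competing event is a cheap improvement

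*Protocol article*

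**What the plan says.** The Statistical analysis section of the protocol article gives two instructions that reach revascularization.

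- A general one: "All secondary endpoint analysis will be performed using the Student’s t-test, chi-square test, or Fisher’s exact test". Under Outcome measures, the secondary endpoints include "5) repeated target lesion revascularization (TLR) rate; 6) repeated target extremity revascularization (TER) rate", so both are due as proportions.
- An additional one for "clinical outcomes such as revascularization of the target vessel, death, major cardiovascular events including myocardial infarction and cerebral infarction, and limb salvage rates": these "will be analyzed using Kaplan-Meier survival estimates and a comparison of the groups will be performed using the log-rank test". Revascularization and death appear as separate items in that list. No competing-event method is named, and the handling of deaths in the revascularization curve is not stated.

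The Appendix defines target lesion revascularization (TLR) and target extremity revascularization (TER) by repeat intervention or bypass surgery, without death as a component. It gives no separate definition of target-vessel revascularization. Limb salvage is defined there so that death counts as an event, and major adverse cardiovascular events (MACE) include all-cause death both there and under Outcome measures.

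On the population, the Study population section admits patients with "moderate or severe intermittent claudication or critical limb ischemia (Rutherford score of 2 to 6", which includes "chronic critical limb ischemia with ischemic ulcers (Rutherford score of 5 to 6"). It excludes "patients with a life expectancy of less than one year due to comorbidities". Under Randomization and interventions, "clinical follow-up will be planned at 1, 6, and 12 months".

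**The concern.** A patient who has died can no longer be revascularized. Kaplan-Meier with deaths censored treats that patient as if still at the same risk as those under follow-up. One minus Kaplan-Meier then estimates the probability of revascularization in a setting where nobody dies. It cannot fall below the cumulative incidence, which is the share of patients revascularized by 12 months, and it exceeds it whenever deaths come before later revascularizations.

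A 12-month revascularization rate is usually read as that share. Because critical limb ischemia is eligible, some deaths within the year are plausible. What is at stake is the absolute level of the Kaplan-Meier revascularization figures as descriptions of stent performance. The test between groups is not at stake: the log-rank test with deaths censored is a valid comparison of cause-specific hazards.

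**Working it through.** **1. The plan's own figure.** The only figure that can be reproduced is the sample size for the primary endpoint. Inputs from Sample size calculation: patency of 65% versus 80%, that is restenosis of 35% versus 20%; 5% significance (two-sided assumed); 80% power; 1:1 allocation. The pooled-variance formula for two proportions without continuity correction gives 138 per group. Dropout of 20%: 138 / 0.80 = 172.5, rounded up to 173 per group, 346 in total. Both match the article. This calculation does not involve Kaplan-Meier.

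**2. Model for the size of the bias.** The article gives neither 12-month mortality nor a revascularization rate, so both are assumed. With constant hazards h1 (revascularization) and h2 (death) over one year:

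- h2 = −ln(1 − mortality)
- cumulative incidence = h1/(h1 + h2) × (1 − exp(−(h1 + h2)))
- Kaplan-Meier complement = 1 − exp(−h1)

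Fix the true cumulative incidence, solve for h1, and compare.

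**3. One case in full.** True rate 20%, mortality 10%:

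- h2 = −ln(0.90) = 0.1054
- h1 = 0.2361, since 0.2361/0.3415 × (1 − exp(−0.3415)) = 0.6914 × 0.2893 = 0.200
- Kaplan-Meier complement = 1 − exp(−0.2361) = 21.0%
- Overstatement = 1.0 point

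**4. Range.**

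| Assumed 12-month mortality | Kaplan-Meier figure, true rate 20% | Overstatement, true 15% | Overstatement, true 20% | Overstatement, true 30% |
|---|---|---|---|---|
| 3% | 20.3% | 0.2 | 0.3 | 0.4 |
| 5% | 20.5% | 0.4 | 0.5 | 0.7 |
| 10% | 21.0% | 0.8 | 1.0 | 1.5 |
| 15% | 21.6% | 1.2 | 1.6 | 2.3 |
| 20% | 22.2% | 1.7 | 2.2 | 3.2 |

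Overstatements are in percentage points.

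**5. Which mortality is plausible?** The document does not say. Suppose 20% to 50% of patients have critical limb ischemia, with assumed 12-month mortality of 10% to 25% in them and 2% to 3% in claudicants. Overall mortality is then 3.6% (0.2 × 10 + 0.8 × 2) to 14% (0.5 × 25 + 0.5 × 3). At a Kaplan-Meier figure of 20%, the overstatement is 0.35 to 1.4 points.

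**6. Against sampling error.** The standard error of a 20% rate is √(0.20 × 0.80/138) = 3.4 points with 138 patients and √(0.20 × 0.80/173) = 3.0 points with 173.

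**7. Effect on a contrast.** Take Kaplan-Meier figures of 35% and 20% as an illustration, with equal mortality in both arms. At 5% mortality the cumulative incidences are 34.2% and 19.5%, so 15.0 points becomes 14.7. At 10% they are 33.3% and 19.0%, so it becomes 14.3.

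**The case against.** The strongest objection is that the Kaplan-Meier analysis is an addition. The sentence before it sends every secondary endpoint, TLR and TER included, to tests on proportions. In a proportion of all randomized patients, someone who dies without revascularization stays in the denominator as a non-event, so this bias does not arise. (How losses to follow-up are handled is a separate question.) This stands. A reader might infer that the trial's reported 12-month revascularization rates will be overstated. The article does not support that, because it does not say which of the two sets of figures will be reported as the rate.

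Second, a reader might infer from the eligibility of critical limb ischemia that mortality will be high and the bias large. The article gives neither the share of such patients nor any mortality, it also admits claudicants, and it excludes life expectancy under one year due to comorbidities. That exclusion lowers expected mortality without removing it, so the 20% row above is the less likely end.

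Third, the rule for deaths may be in an analysis plan that is not shown. That is fair as to detail. But the article itself names the estimator, and ordinary Kaplan-Meier for an endpoint that excludes death censors deaths.

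Fourth, the risk of device failure among patients still alive is a defensible quantity for comparing stents. That is so, and it is why the log-rank comparison should stay. It does not make one minus Kaplan-Meier the share of patients revascularized.

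**Conclusion.** The point holds as a minor one. The Kaplan-Meier revascularization estimates, as planned, would be slightly too high. At a true rate of 20% the overstatement is about 0.3 to 1.0 points for 12-month mortality of 3% to 10%, and about 2 points only near 20%. These figures rest on assumed rates and constant hazards. Over the 3% to 10% range the bias is at most about a third of one arm's standard error.

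It does not reach the primary endpoint, which is compared by chi-square or Fisher, or the sample size, which reproduces. MACE and limb salvage already count death as an event. The log-rank tests stand. If mortality differed between groups, the bias in the rates would differ too, but nothing in the article indicates such a difference. No conclusion of the trial would be expected to change.

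**What to change.** Change the Kaplan-Meier sentence in the Statistical analysis section so that target lesion, target vessel and target extremity revascularization are summarized by the cumulative incidence function, with death as a competing event, in place of one minus Kaplan-Meier. Keep the log-rank test for these outcomes and label it a comparison of cause-specific hazards. Keep Kaplan-Meier for death, limb salvage and composites that include death.

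The cost is one sentence in the plan and a few lines of code. The one downside is that SPSS 20.0, the program named for all analyses, may need a supplementary package for the estimate. Sample size and data collection do not change.
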